## LIST OF ABBREVIATIONS AND RELEVANT DEFINITIONS

|                |                                                                                                                                                                                                                                                                                                                                           |
|----------------|-------------------------------------------------------------------------------------------------------------------------------------------------------------------------------------------------------------------------------------------------------------------------------------------------------------------------------------------|
| ABR     | ABR form, General Assessment and Registration form, is the application form that is required for submission to the accredited Ethics Committee (In Dutch, ABR = Algemene Beoordeling en Registratie)                                                                                                                                      |
| AE      | Adverse Event                                                                                                                                                                                                                                                                                                                             |
| BNSS    | Brief Negative Symptom Scale                                                                                                                                                                                                                                                                                                              |
| CCMO    | Central Committee on Research Involving Human Subjects; in Dutch: Centrale Commissie Mensgebonden Onderzoek                                                                                                                                                                                                                               |
| IOA     | Inventarisatielijst omgaan met anderen                                                                                                                                                                                                                                                                                                    |
| ISMI    | Internalized Stigma of Mental Illness                                                                                                                                                                                                                                                                                                     |
| IVM     | Integrale veiligheidsmonitor                                                                                                                                                                                                                                                                                                              |
| MANSA   | Manchester Short Assessment of Quality of Life                                                                                                                                                                                                                                                                                            |
| METC    | Medical research ethics committee (MREC); in Dutch: medisch ethische toetsing commissie (METC)                                                                                                                                                                                                                                            |
| MST     | Modified Shuttle Test                                                                                                                                                                                                                                                                                                                     |
| NWO     | Nederlandse organisatie voor Wetenschappelijk Onderzoek                                                                                                                                                                                                                                                                                   |
| PANSS   | Positive And Negative Symptoms Syndromes                                                                                                                                                                                                                                                                                                  |
| PMT     | Psychomotor therapy                                                                                                                                                                                                                                                                                                                       |
| PTSD    | Post-Traumatic Stress Disorder                                                                                                                                                                                                                                                                                                            |
| RCT     | Randomized Controlled Trial                                                                                                                                                                                                                                                                                                               |
| SERS-SF | Self-Esteem Rating Scale – Short Form                                                                                                                                                                                                                                                                                                     |
| SIG     | Schaal Interpersoonlijk Gedrag                                                                                                                                                                                                                                                                                                            |
| SFS     | Social Functioning Scale                                                                                                                                                                                                                                                                                                                  |
| Sponsor | The sponsor is the party that commissions the organisation or performance of the research, for example a pharmaceutical company, academic hospital, scientific organisation or investigator. A party that provides funding for a study but does not commission it is not regarded as the sponsor, but referred to as a subsidising party. |
| CTS2    | Revised Conflict Tactics Scale                                                                                                                                                                                                                                                                                                            |
| TSQ     | Trauma Screening Questionnaire                                                                                                                                                                                                                                                                                                            |
| Wbp     | Personal Data Protection Act (in Dutch: Wet Bescherming Persoonsgegevens)                                                                                                                                                                                                                                                                 |
| WMO     | Medical Research Involving Human Subjects Act (in Dutch: Wet Medisch-wetenschappelijk Onderzoek met Mensen)                                                                                                                                                                                                                               |
| ZECV    | Self-Expression and Control                                                                                                                                                                                                                                                                                                               |

## SUMMARY

### Rationale

Contrary to what is generally thought, people with psychotic disorders are more likely to be a victim of a crime, than an offender. Research has revealed several factors to be associated with victimization in patients with psychotic disorder. Impaired social cognition, decreased insight and problems in aggression regulation may lead to inadequate social behavior which increases the risk of victimization. In turn victimization can increase self-stigma resulting in reduced self-esteem, empowerment, and assertiveness, making patients more vulnerable for victimization. In addition, the traumatic experience of the victimization could induce strong physiological responses to external stimuli resulting in fear regulation problems. Consequently, becoming a victim significantly enhances risk for revictimization. The aim of this study is to investigate a new intervention which addresses the risk factors that may help prevent victimization of people with psychotic disorders.

### Objective:

The proposed study aims to investigate the effects of a psychomotor assertiveness training by means of a multicentre randomized controlled trial (RCT). Effects will be examined at the behavioural level by means of questionnaires and interviews, and at the cerebral level with an fMRI task. The effect on actual victimisation will be investigated as a long term outcome, because the prevalence of incidents is low thus we expect that effects of the intervention will only be visible after a longer period of time. Short term effects on risk factors of victimization (e.g. social cognition, self-stigma, assertiveness, self-esteem, aggression regulation, social behaviour) will be examined, since these are direct targets of the intervention. We expect that the risk factors will mediate the effect between the training and victimization.

### Study design

To test the effectiveness of the intervention, an RCT with a pretest-posttest and follow-up will be performed.

### Study population

120 participants will be recruited from GGZ Drenthe, GGZ Friesland, GGZ Centraal, Lentis, UCP, Arkin and Dimence. Twenty-two participants per condition will be included in the fMRI part of the study. Onsite therapists will select the potentially eligible patients using seven screening questions.

**Intervention**

A psychomotor assertiveness training with elements of kickboxing aims to decrease the risk of victimization. The training consists of 20 weekly group training sessions divided into five modules (see 5.1.1 for a description of the modules). Each session takes 75 minutes. Groups contain a maximum of ten participants.

**Main study parameters/endpoints**

Primary study outcome is the long term effect of the psychomotor assertiveness training with elements of kickboxing on victimization, as measured by two questionnaires which examine whether an individual has been victim of a crime. We expect that this effect will be mediated by risk factors of victimization (e.g. social cognition, internal stigma, assertiveness, self-esteem, aggression regulation, social behaviour), as measured by both behavioural and cognitive measures such as interviews, questionnaires and a neuropsychological test, and cerebral measures such as fMRI paradigms. Secondary long term outcome measures are quality of life, recovery, social participation, negative symptoms and coping with trauma.

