#### 6.1.2 Main study parameters/end point

The main study parameters and subsequent instruments used in this study are shown in table 4.

Table 4: Main study parameters

| Parameter                         | Instrument                 | Duration   | Type                     |
|-----------------------------------|----------------------------|------------|--------------------------|
| Primary outcome measures   |                            |            |                          |
| Victimization                     | IVM                        | 10 minutes | Self-rating              |
|                                   | CTS2                       | 20 minutes | Self-rating              |
| Mediating factors          |                            |            |                          |
| Social cognition                  | Faux pas task              | 20 minutes | Neuropsychological task  |
|                                   | Wall of faces task**       | 20 minutes | fMRI task                |
|                                   | Emotional faces paradigm** | 15 minutes | fMRI task                |
| Self-expression and control       | ZECV                       | 10 minutes | Self-rating              |
| Internalised stigma               | ISMI                       | 15 minutes | Self-rating              |
| Social behavior                   | SIG                        | 15 minutes | Self-report              |
| Self-esteem                       | SERS-SF                    | 10 minutes | Self-rating              |
| Secondary outcome measures |                            |            |                          |
| Quality of life                   | MANSA                      | 5 minutes  | Self-rating              |
| Trauma                            | TSQ                        | 5 minutes  | Self-rating              |
| Recovery                          | NHS                        | 10 minutes | Self-rating              |
| Societal participation            | SFS                        | 20 minutes | Self-report              |
| Negative symptoms                 | BNSS in addition to PANSS  | 30 minutes | Semistructured interview |
| Fitness                           | MST                        | 15 minutes | Physical test            |
| Physical activity                 | Accelerometer              | 1 week     | Physical measure         |

\*IVM= Integrale Veiligheidsmonitor

CTS2= Revised Conflict Tactics Scale

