### **Integrale Veiligheidsmonitor**

The Integrale Veiligheidsmonitor (IVM) is a Dutch crime and victimization survey that resembles the international crime victimization survey (CBS, 2009). We will use the victimization subscale (Victrom: Kamperman et al., 2014) and the subscales about safety perception in general and in one's neighborhood. Participants will complete the IVM pre- and post- treatment as well as during both follow up assessments, since we are particularly interested in victimization in the long term. The time-frame in the questions will be adapted, in order to investigate victimization between two subsequent assessment points. At baseline, the time-frame consists of the past five years. At both post assessments, victimization of past six months will be examined. At follow-up victimization of the past year will be assessed.

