### **Revised Conflict Tactics Scale**

The revised Conflict Tactics Scale (CTS2) measures to what extent the respondent is involved in a psychological or physical attack and the use of reasoning or negotiation to deal with conflicts (Straus, Hamby, Boney-McCoy, & Sugarman, 1996). The CTS2 is a widely used instrument in partner violence research and consist of 39 behavior items. Participants report how many times, ranging from 1 'has never happened' to 8 'more than twenty times' the items apply on themselves or their partner in a given time period (Vega & O'Leary, 2007). Since we are interested in a broader range of social interactions we changed the questions from 'partner' to 'someone'. For example 'I kicked my partner' and 'My partner did this to me' is changed in 'I kicked someone' and 'Someone did this to me'. The CTS2 assesses more subtle forms of victimization, therefore this instrument is a good addition to the IVM.

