### 8.2 Analysis

The effect of the training on long term victimization (primary study parameter) and on general long term outcomes, will be investigated by means of a repeated measures fixed-effects analysis of variance (ANOVA). The effect on risk factors of victimization (second study parameter) will be tested using multilevel modelling with the pre- and posttest and follow-up on the first level and training condition on the second level (o.a. Snijders & Bosker, 2000). A model will be constructed for every dependent variable and the dependent variables will be adjusted for covariates. Statistical analysis will be conducted using the IBM SPSS Statistics package. Dummy variables will be constructed for every level and the statistical significance of the regression-effects will be tested using the T-test. The dummy-variables and their interaction will be added to the model as fixed effects. The level of significance is set at  $p < 0.05$ , two-sided.

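### IVM and CTS2 are two unranked primary measures under one undivided 0.05, with no rule for which decides; CTS2 as described is also not purely a victimisation score

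*Protocol*

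**What the plan says.** - **Summary, Main study parameters/endpoints:** the primary outcome is the long-term effect on victimisation, "as measured by two questionnaires which examine whether an individual has been victim of a crime".
- **Section 6.1.2, Table 4:** IVM and CTS2 both stand under "Primary outcome measures", against the single parameter victimisation. Neither is ranked above the other.
- **Section 8.2:** the effect on long-term victimisation "will be investigated by means of a repeated measures fixed-effects analysis of variance (ANOVA"). The section does not say whether this is one combined score or two outcomes. The only decision threshold is general: "The level of significance is set at $p < 0.05$ , two-sided".
- **Section 6.1.2, Integrale Veiligheidsmonitor:** the trial uses the victimisation subscale and also "the subscales about safety perception in general and in one's neighborhood".
- **Section 6.1.2, Revised Conflict Tactics Scale:** the instrument covers attacks and also reasoning and negotiation. Its example items pair an act by the respondent with the same act done to the respondent. The section concludes that "this instrument is a good addition to the IVM".

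**The concern.** There are two distinct problems.

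**Decision rule.** With two primary measures, one undivided 0.05 and no rule, the sponsor could read a significant result on either questionnaire as success of the trial. The error rate of that claim would then exceed the 5% that section 8.2 appears to promise. A split result, with one instrument significant and the other not, would have no agreed interpretation.

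**Meaning of the score.** The Summary describes both questionnaires as asking whether the person was a crime victim. The CTS2 section describes something broader. This matters here because the training itself teaches de-escalation (module 2) and aggression regulation (module 4), and the Summary names aggression regulation as a mediator. A CTS2 total containing the respondent's own acts could fall because the respondent became less aggressive, with no change in being victimised. Negotiation items are not harms at all, and more negotiation could push a simple total in the opposite direction.

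**Working it through.** **Inputs from the protocol.** Two primary instruments (Summary; Table 4). Two-sided alpha 0.05 (section 8.2). Effect size 0.50, power 0.80, 25% drop-out and 60 per group (sample size calculation). The correlation between the two test statistics is not given, so I assume a range of 0 to 0.9.

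**The plan's own figure.** The protocol states no error rate for the primary claim beyond the 0.05 level, so there is none to reproduce. Its sample size of 60 per group uses one effect size and one alpha and is tied to neither instrument. A two-sample t-test at d = 0.50 needs 64 evaluable per arm, and 64/0.75 = 85.3, so 86 per arm. The stated 60 does not reproduce from the stated inputs. That is a separate matter and does not bear on this point. I take from it only 60 × 0.75 = 45 evaluable per arm.

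**Step 1: either instrument suffices, each tested at 0.05, independent tests.**
1 − (1 − 0.05)² = 1 − 0.9025 = 0.0975.

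**Step 2: the same with correlated tests.** Under the joint null, with (Z1, Z2) bivariate normal with correlation r, the error rate is 1 − P(|Z1| < 1.96 and |Z2| < 1.96). The chance that both are significant is 0.05 + 0.05 minus that value.

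| Assumed r | Either significant | Ratio to 0.05 | Both significant |
|---|---|---|---|
| 0 | 0.0975 | 1.95 | 0.0025 |
| 0.3 | 0.0951 | 1.90 | 0.0049 |
| 0.5 | 0.0907 | 1.81 | 0.0093 |
| 0.7 | 0.0835 | 1.67 | 0.0165 |
| 0.9 | 0.0704 | 1.41 | 0.0296 |

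**Step 3: both instruments required.** Under the joint null the error rate is the last column, always below 0.05. If only one null is true, the claim still needs that true null to be rejected, so the rate cannot exceed 0.05. There is no inflation under this rule.

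**Step 4: cost of working at 0.025.** Two independent tests at 0.025 give 1 − 0.975² = 0.0494. At d = 0.50 with 45 evaluable per arm, t-test power is 0.65 at alpha 0.05 and 0.54 at alpha 0.025. Reaching 0.80 at 0.025 takes 78 evaluable per arm, or 78/0.75 = 104 with drop-out.

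**Step 5: content, side by side.** The Summary says both questionnaires examine whether someone was a crime victim. The IVM section names a victimisation subscale that fits this, with safety perception alongside it. The CTS2 section lists acts suffered, which fit, and also own acts and negotiation, which do not. No section says which items form the primary score.

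**The case against.** The strongest reply is that separate testing of each instrument is inferred. Section 8.2 speaks of victimisation as one parameter, and its sentence "A model will be constructed for every dependent variable" follows directly on the multilevel plan for the risk factors. A reader might take it to mean that each primary instrument has its own model at 0.05. The text does not establish that, and it leaves a combined score or a both-required rule open. This stands, and it is why the inflation has to be stated conditionally.

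A reader might also conclude that the false-positive rate simply doubles. That is close to true only if either instrument suffices and the tests are near independence. Two self-reports of related experiences are plausibly positively correlated, which lowers the figure.

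A third tempting step is to count the IVM safety-perception subscales as further primary tests and arrive at a larger error rate. Nothing supports this. Table 4 gives the primary parameter as victimisation, and the IVM section keeps its victimisation subscale apart from the safety subscales. Mixed content affects what a score means, not the error rate of two tests.

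It is also fair that no section makes the CTS2 total the endpoint, and that scoring and multiplicity detail often sits in a statistical analysis plan, which is not shown here. What remains does not depend on such a plan. The protocol itself names two equal primary measures at one undivided level, and its Summary describes CTS2 more narrowly than its own methods section does.

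Finally, calling CTS2 an addition to the IVM may mean complementary and not subordinate. That is a reason to offer the sponsor a choice of rule.

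**Conclusion.** The point holds in conditional form. The protocol fixes two unranked primary measures and one undivided two-sided 0.05, without saying which instrument, or what combination, decides the trial. If success on either suffices, the false-positive rate of the primary claim is at most 9.75%, and about 9.5% to 8.3% for correlations of 0.3 to 0.7. These correlations are assumptions, since the protocol gives none. If both must succeed, the rate is not inflated.

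Separately, the Summary's description of the primary questionnaires does not match the CTS2 section. A CTS2 total, if that were used, would not be a victimisation score. Both matters should be settled in the protocol text before outcome data are examined.

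**What to change.** Amend the Summary endpoint paragraph, Table 4 and section 8.2 together.

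1. **State a rule that holds the primary claim at 0.05.** Either test the IVM victimisation subscale first at two-sided 0.05, and CTS2 at 0.05 only if the IVM is significant, or, if the sponsor wants the instruments equal, apply Holm: the smaller p-value against 0.025, then the other against 0.05.
2. **Define the primary scores.** Use the IVM victimisation subscale and only those CTS2 items that record acts done to the respondent. Move safety perception, CTS2 own acts and CTS2 negotiation to secondary.

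No new data are needed. Under the fixed sequence the IVM keeps the full 0.05, but CTS2 can no longer carry the claim alone, which matters because it was included to capture subtler victimisation. Under Holm either instrument can carry the claim, at the price of the power loss at the 0.025 step shown in the working (0.65 to 0.54).
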